## Background

Cerebellar disease results in well-known motor performance deficits, including ataxia of stance and gait, limb incoordination, dysarthria, and oculomotor abnormalities. During the last decades, there has been growing evidence that cerebellar disease is not only accompanied by motor disturbances but also by cognitive and affective symptoms (see [1–3] for reviews). As early as 1998, Schmahmann and Sherman introduced the *Cerebellar Cognitive Affective/ Schmahmann Syndrome (CCAS)* [4]*.* The core symptoms of CCAS are difficulties with executive, linguistic and visuospatial functions as well as problems with the regulation of emotion and affect. Since its original description, evidence for the presence of CCAS has been accumulating in pediatric and adult patients suffering from different cerebellar diseases including various hereditary ataxias, cerebellar tumors, and cerebellar stroke [1–3]. In recent years, advances in structural and functional brain imaging allowed for detailed mapping of cognitive functions in the posterolateral cerebellar hemisphere [5–9]. As yet, diagnosis of CCAS relies on non-standardized bedside cognitive examination and, if available, detailed neuropsychological test batteries. Until recently, there has not been a validated bedside test that was able to reliably screen for CCAS in cerebellar patients – unlike well-established bedside tests for dementias or mild cognitive impairment (MCI), i.e. Mini Mental State Examination (MMSE) or Montreal Cognitive Assessment (MoCA). However, MMSE and MoCA are of limited use to screen for CCAS because cerebellar patients frequently perform within the normal range [10]. Recently, Schmahmann and colleagues [10] have developed a bedside test designed to screen for CCAS in adults. In order to develop this CCAS Scale, they first applied a broad battery of 36 well-established neuropsychological tests in a large group of cerebellar patients primarily suffering from cerebellar degeneration. In the novel CCAS Scale, tests were implemented which captured the core cognitive domains of CCAS, distinguished best between cerebellar patients and controls, and at the same time were short and easy enough to be applied in a bedside setting. These include test items for semantic and phonemic fluency, category switching, verbal registration and delayed verbal recall, digit span forward and backward, cube draw and copy, similarities, go/ no-go, and affect. Single tests can either be passed reaching a specific cut-off score or failed. CCAS is considered possible if one test is failed, probable if two tests are failed, and definite if three or more tests are failed. Version A of the CCAS Scale has then been validated in another US-American cohort of 39 adult cerebellar patients, including patients with cerebellar degeneration and focal cerebellar lesions and 55 matched healthy controls. It exhibited high values for selectivity [that is the ability to distinguish between patients and controls, or in other words preventing controls from being diagnosed as patients; possible/ probable/ definite CCAS: 78/ 93/ 100%] and reasonable sensitivity [that is the probability that a patient is identified as a patient; possible/ probable/ definite CCAS: 95/ 82/ 46%]. Furthermore, it showed modest internal consistency using Cronbach’s alpha value (= 0.59) indicating that no test item within the scale measures the exact same domain(s) as another item. Thus, no test item is redundant. Comparing patients with pure cerebellar lesions and patients with additional extracerebellar involvement the authors found that difficulties in verbal registration and delayed verbal recall were more prominent in the latter. Therefore, poor performance in these two test items is indicative of extracerebellar involvement (“red flag”). In addition to the pass/ fail criteria which are used to screen for CCAS, a total sum score is calculated which allows for follow-up examinations in individual patients [10]. Three parallel versions B-D were developed to enable repeated assessments. In the present study preliminary German versions of the CCAS Scale are introduced, and the study protocol for their validation is presented.

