##### Assessment of the CCAS Scale

The CCAS Scale will be administered in each participant at least once. In the validation process of version A, at least 40 patients and 40 controls will receive a follow-up examination with the same version of the scale to determine test-retest and interrater reliability (≥ 20 patients and ≥ 20 controls, respectively). Retesting will be done with the same version because equivalence of versions A-D has not yet been shown (see [10] and Supplements). Follow-up will take place within an interval of 14 to 56 days. A time interval is favored instead of a fixed time span between test and retest (e.g. exactly 14 days) to control for learning effects by correlating retest results with different retest time intervals.

To assess construct validity of the German version of the CCAS Scale a detailed neuropsychological testing will be done in a subset of patients (*n* ≥ 20) and controls (*n* ≥ 20) using well-established neuropsychological test batteries available in German. These will comprise the logical memory test (part I and II) of the Wechsler Memory Scale – 4th edition (WMS-IV) [18], the copy immediate and delayed recall of the Rey–Osterrieth Complex Figure Test (ROCFT) [19], and the letter-number sequencing task of the WAIS-IV [20]. These tests measure the same cognitive domains as corresponding items of the CCAS Scale. Furthermore, the German version 3 of the MoCA [21] will be assessed for direct comparison with the CCAS Scale. Finally, the Patient Health Questionnaire (PHQ-9) [22] and the German version of the EuroQuol – 5 dimension – 3 level (EQ-5D-3L) questionnaire [23] will be administered.

Validation of parallel versions of the CCAS Scale will be done the same way as for validation of parallel German versions of the MoCA [21]. Each parallel version (B/C/D) of the CCAS Scale will be tested against version A. Testing of version B/C/D and version A will be done on the same day, with the order being randomized between participants.

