##### Data analysis

Selectivity and sensitivity will be assessed using the same cut-off values for individual test items, and the same three pass/ fail criteria determined in the original study by Hoche et al. [10] (that is: possible CCAS = one test failed; probable CCAS = two tests failed; definite CCAS = three or more tests failed). To assess selectivity the percentage of true negatives will be calculated, that is the percentage of controls which have been correctly identified as controls [number of controls identified as controls/ true number of controls in the sample * 100]. To assess sensitivity the percentage of true positives will be calculated, that is the percentage of patients which have been correctly identified as patients [number of patients identified as patients/ true number of patients in the sample * 100]. In case selectivity and sensitivity falls below the values of the original CCAS Scale, selectivity and sensitivity of individual tests will be assessed. Cut-off values of single test items and/ or cut-offs defining (possible/ probable/ definite) CCAS will be adjusted to achieve high selectivity and reasonable sensitivity – comparable to the values of the original CCAS Scale.

Differences between patient groups (pure cerebellar disease vs. patients with additional extracerebellar involvement) will also be analyzed. We want to verify that difficulties in verbal registration and delayed verbal recall are indicative of extracerebellar involvement (“red flags”). In further accordance with Hoche et al. [10], Cronbach’s alpha will be used to assess the inter-relatedness of the individual test items, i.e. internal consistency.

To study construct validity of the CCAS Scale subtests of validated German versions of neuropsychological test batteries will be used as the external criterion. We will compare the percentage of patients diagnosed with CCAS based on a detailed neuropsychological test battery with the percentage of patients identified by the CCAS Scale.

Finally, correlations between age, disease duration, severity of cerebellar motor symptoms (measured by clinical ataxia scores), and total CCAS sum score will be calculated. All raw data (thus total number of failed tests respective total sum score and sub scores on single test items) will be tested for normal distribution using Kolmogorov-Smirnov tests. Parametric or non-parametric tests will be applied depending on distribution and final sample size.

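### The neuropsychological battery has no counterpart for six CCAS Scale items, so comparing percentages diagnosed cannot show construct validity of the whole scale

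*Protocol article*

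**What the plan says.** The Background of the protocol article defines the construct: "The core symptoms of CCAS are difficulties with executive, linguistic and visuospatial functions as well as problems with the regulation of emotion and affect". It lists the scale's items as "semantic and phonemic fluency, category switching, verbal registration and delayed verbal recall, digit span forward and backward, cube draw and copy, similarities, go/ no-go", and the list closes with "similarities, go/ no-go, and affect". One failed test gives possible, two give probable, and three or more give definite CCAS, whichever tests they are. On verbal registration and delayed recall, it says that "poor performance in these two test items is indicative of extracerebellar involvement".

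Assessment of the CCAS Scale describes the detailed testing of at least 20 patients and at least 20 controls. It consists of "the logical memory test (part I and II) of the Wechsler Memory Scale", the complex figure test (copy, immediate and delayed recall) and letter-number sequencing. The article comments: "These tests measure the same cognitive domains as corresponding items of the CCAS Scale". The MoCA, PHQ-9 and EQ-5D-3L are listed after this, separately from the battery.

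Data analysis states that "subtests of validated German versions of neuropsychological test batteries will be used as the external criterion". The comparison it specifies sets the share of patients given a CCAS diagnosis from the battery against the share picked up by the scale. It specifies no item-level comparison.

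**The concern.** An external criterion for a whole scale has to cover what the scale covers. The scale's diagnosis counts failures across all its items, while the named battery addresses only some of them. If the two methods give different percentages, the cause may be the choice of battery tests and not a weakness of the German scale. If they give similar percentages, the battery and the scale may still be picking out different patients for different reasons.

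At stake is the construct-validity claim, which the Abstract lists among the planned parts of the validation. Several of the items left without a criterion (the two fluency items, switching, similarities) are verbal, so a translated scale has particular need of outside evidence on them.

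**Working it through.** The plan states no coverage figure to reproduce. The check is a mapping of the items in the Background to the tests in Assessment of the CCAS Scale, followed by a count.

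**Step 1. Map items to tests.** The article gives no item-by-item map, so the pairings below are inferred from the names of the tests. Doubtful cases are resolved in the plan's favour.

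| CCAS Scale item | Counterpart in the battery |
|---|---|
| Semantic fluency | none |
| Phonemic fluency | none |
| Category switching | none |
| Verbal registration | logical memory |
| Delayed verbal recall | logical memory |
| Digit span forward | letter-number sequencing (generous) |
| Digit span backward | letter-number sequencing (generous) |
| Cube (draw and copy) | complex figure copy |
| Similarities | none |
| Go/no-go | none |
| Affect | none |

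**Step 2. Count the items.** With the cube as one item there are 11, of which 5 have a counterpart and 6 do not: 6/11 = 55%. With cube draw and cube copy as two items there are 12, of which 6 have a counterpart and 6 do not: 6/12 = 50%. The same six are uncovered either way.

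**Step 3. Count the battery scores.** These are logical memory I, logical memory II, figure copy, figure immediate recall, figure delayed recall and letter-number sequencing, which makes 6. The two logical memory scores and the two figure recall scores are memory scores: 4/6 = 67%. The figure-test phrase in the article is unpunctuated. If it means recall only, the memory share is 4/5 = 80% and the cube loses its counterpart too. The main count uses the reading that favours the plan.

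**Step 4. Compare with the construct.** The core domains in the Background are executive, linguistic, visuospatial and affective. Memory is not among them. The scale does contain two verbal memory items, but the Background reads poor performance on them as a sign of extracerebellar involvement. Most of the battery's scores therefore lie outside the listed core domains.

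**Step 5. Apply the diagnostic rule.** Definite CCAS needs three failed tests, and six items are uncovered. A patient who fails both fluency items and category switching is definite on the scale, and no battery test targets any of those functions. The battery may be entirely normal in such a patient.

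**Step 6. See what two percentages can show.** Suppose n patients have both assessments and each method marks k of them positive. The number positive on both can lie anywhere from max(0, 2k − n) to k. At the minimum n = 20, and with k = 10 chosen only for illustration, the range is from max(0, 20 − 20) = 0 to 10. Identical percentages of 50% are then compatible with no overlap at all and with complete overlap. Where the two methods sample different functions, as here, equal percentages cannot be taken as evidence of a shared construct.

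**The case against.** **The sentence about corresponding items is accurate.** A reader might infer that the article wrongly claims the battery matches the whole scale. It does not: "These tests measure the same cognitive domains as corresponding items of the CCAS Scale" is limited to items that have a counterpart and is not false. The difficulty arises only when Data analysis applies the battery to the whole-scale diagnosis.

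**The limitations are disclosed.** The Perspective section says that construct validity is tested only in a subset and that no standard criteria exist for diagnosing CCAS from detailed testing. It also says that the affect item depends on the examiner's expertise and that expert neuropsychiatric assessment would be a useful further criterion in future. The remark on affect stands and covers part of the gap for that item. Nothing there says that fluency, switching, similarities and go/no-go are absent from the battery, and agreed diagnostic criteria could not recover functions that were not measured.

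**Other instruments are given.** The MoCA is planned as a direct comparator, not as the external criterion, and the Background calls it of limited use because cerebellar patients often score in the normal range. The PHQ-9 is identified in the abbreviations as a depression questionnaire and has no stated role in the criterion. It could be a partial comparator for affect at most.

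**Memory-only patients.** A reader might infer that a patient with memory loss alone would be abnormal on the battery and normal on the scale. The documents do not support this. Registration and delayed recall are scale items, so failing one gives possible CCAS and failing both gives probable CCAS.

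**Case mix.** A reader might also carry over the planned share with extracerebellar involvement (at least 40 of 65, 62%) to argue that memory failures will dominate the comparison. That share describes the version A cohort. No mix is stated for the subset of at least 20 patients.

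**More than half the scale.** This depends on counting the cube once. Counted as two items, exactly half is uncovered. The article gives no item total, and the figure showing the form is not available here.

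**The primary aim is untouched.** This is correct. The Perspective section gives selectivity as the primary aim, and that analysis does not use the battery.

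**Conclusion.** The point stands in this form: the named battery cannot serve as external criterion for the whole CCAS Scale, and the comparison of percentages in Data analysis would not be evidence of construct validity whichever way it came out. Six items lack a counterpart (55% of 11, or 50% of 12), and four of the six battery scores are memory scores although memory is not a listed core domain.

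This rests on the item list in the Background, on pairings inferred from test names, and on the generous match of letter-number sequencing to digit span. A stricter mapping would widen the gap. It does not rest on any assumption about who will be in the tested subset.

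The consequence is limited to the construct-validity claim. Selectivity, sensitivity and reliability are not affected. The change is still worth making, because the matched-item analysis uses data that will be collected anyway and prevents a conclusion that the design cannot support.

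**What to change.** In Data analysis:

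- Define construct validity as a within-patient, item-level convergent analysis of the matched pairs: verbal registration and delayed recall with logical memory, the cube with complex figure copy, and digit span with letter-number sequencing.
- Keep the whole-scale comparison of percentages as descriptive only, and say that it is not evidence of construct validity.
- State that semantic and phonemic fluency, category switching, similarities and go/no-go have no external criterion in this study.
- State that the PHQ-9 is at most a partial, exploratory comparator for the affect item.

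In Assessment of the CCAS Scale, name the item to which each battery test corresponds. This adds detail to a sentence that is otherwise correct.

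The cost is wording and a narrower construct-validity claim. No new tests, visits or participants are needed. With a minimum of 20 patients the item-level estimates will be imprecise, so they should be given with confidence intervals.

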##### Data analysis

Selectivity and sensitivity will be assessed using the same cut-off values for individual test items, and the same three pass/ fail criteria determined in the original study by Hoche et al. [10] (that is: possible CCAS = one test failed; probable CCAS = two tests failed; definite CCAS = three or more tests failed). To assess selectivity the percentage of true negatives will be calculated, that is the percentage of controls which have been correctly identified as controls [number of controls identified as controls/ true number of controls in the sample * 100]. To assess sensitivity the percentage of true positives will be calculated, that is the percentage of patients which have been correctly identified as patients [number of patients identified as patients/ true number of patients in the sample * 100]. In case selectivity and sensitivity falls below the values of the original CCAS Scale, selectivity and sensitivity of individual tests will be assessed. Cut-off values of single test items and/ or cut-offs defining (possible/ probable/ definite) CCAS will be adjusted to achieve high selectivity and reasonable sensitivity – comparable to the values of the original CCAS Scale.

Differences between patient groups (pure cerebellar disease vs. patients with additional extracerebellar involvement) will also be analyzed. We want to verify that difficulties in verbal registration and delayed verbal recall are indicative of extracerebellar involvement (“red flags”). In further accordance with Hoche et al. [10], Cronbach’s alpha will be used to assess the inter-relatedness of the individual test items, i.e. internal consistency.

To study construct validity of the CCAS Scale subtests of validated German versions of neuropsychological test batteries will be used as the external criterion. We will compare the percentage of patients diagnosed with CCAS based on a detailed neuropsychological test battery with the percentage of patients identified by the CCAS Scale.

Finally, correlations between age, disease duration, severity of cerebellar motor symptoms (measured by clinical ataxia scores), and total CCAS sum score will be calculated. All raw data (thus total number of failed tests respective total sum score and sub scores on single test items) will be tested for normal distribution using Kolmogorov-Smirnov tests. Parametric or non-parametric tests will be applied depending on distribution and final sample size.

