**Perspective:**

The overall aim is to deliver a validated bedside test to screen for CCAS in German-speaking patients which can also be used in future natural history and therapeutic trials.

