##### Demographics and clinical assessment of cerebellar motor syndrome

Demographics including years of education and employment, educational achievements as well as occupational and marital status will be recorded. For patients, medical records and available brain scans will be evaluated. Age of onset, disease duration and in case of genetically proven nucleotide repeat diseases the repeat length will be documented. Furthermore, a detailed medical history will be taken, and a neurological examination will be performed in every participant. Severity of cerebellar ataxia in patients will be evaluated using different clinical ataxia scales: The Scale for the Assessment and Rating of Ataxia (SARA) [13] will be used because of its widespread use. In addition, the International Cooperative Ataxia Rating Scale (ICARS) [14] will be used because it includes rating of cerebellar oculomotor deficits. Its short form – BARS – [15] will be used to enable direct comparison with the original US-American validation study. The SpinoCerebellar Ataxia Functional Index (SCAFI) [16] will be assessed because it allows for a more objective quantification of motor deficits. Finally, non-ataxia signs will be assessed semi-quantitatively using the Inventory of Non-Ataxia Signs (INAS) [17].

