We are interested whether the scale is able to screen for CCAS in patients with degenerative diseases, but also suffering from cerebellar stroke or surgical lesions due to cerebellar tumors. In the validation study of the original American English CCAS Scale only few patients with focal cerebellar lesions were tested [10]. In part of the patients with focal lesions brain MRI scans will be available. This will allow to map dysfunction in the different cognitive domains to lesions in specific cerebellar regions. For example, we expect that language dysfunction is associated with lesions of the right posterolateral cerebellar hemisphere, and visuospatial disabilities with lesions of the left posterolateral cerebellar hemisphere [6].

A limitation of the CCAS Scale is that detection of the neuropsychiatric abnormalities highly depends on the examiner’s expertise. The authors of the US-American original were aware of this weakness and gave this item (“Affect”) a weak denominator for the total sum score [10]. Additionally, administration of more detailed scales of neuropsychiatric dysfunction are recommended [24]. In future studies, expert neuropsychiatric assessments would be of interest as a further external criterion. Furthermore, testing of construct validity has some limitations. We will perform detailed neuropsychological testing only in a subset of patients. More importantly, although the core symptoms of CCAS are well described, as yet there are no standard criteria to diagnose CCAS based on detailed neuropsychological testing. Another approach to test construct validity would be to compare CCAS scores in patients with cerebellar diseases and patients with non-cerebellar neurological diseases in the future. Despite these limitations the CCAS Scale has been shown to be more sensitive to detect cognitive and affective changes in cerebellar disease than the Mini-Mental State Examination and the Montreal Cognitive Assessment [10]. The validated German CCAS Scale will allow trained healthcare personnel to screen for cognitive and affective symptoms in patients with cerebellar diseases in German-speaking countries.

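### The planned sensitivity is the share of all cerebellar patients who score positive, not sensitivity for CCAS, and a shortfall in it alone should not lead to new cut-offs

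*Protocol article*

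**What the plan says.** The overall aim, in the Perspective paragraph of the abstract, is to "deliver a validated bedside test to screen for CCAS in German-speaking patients". The closing Perspective section of the article gives the same use and places it in people who already have a cerebellar disease.

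The Data analysis section defines two accuracy figures. Sensitivity is "number of patients identified as patients/ true number of patients in the sample * 100". Selectivity is "number of controls identified as controls/ true number of controls in the sample * 100". The Background reads the US results in the same way and reports sensitivity as "possible/ probable/ definite CCAS: 95/ 82/ 46" per cent and selectivity as "possible/ probable/ definite CCAS: 78/ 93/ 100" per cent. The Methods paragraph of the abstract makes comparability with these US values the test of the German version.

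Under Inclusion and exclusion criteria and Study sample, patients are enrolled by degenerative cerebellar diagnosis or focal lesion: at least 25 cer-pure and at least 40 cer-plus. CCAS is not an entry criterion.

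If the figures fall below the US values, Data analysis first looks at individual tests. It then adjusts item cut-offs, the CCAS pass/fail cut-offs, or both, until the results are comparable with the US ones.

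**The concern.** The reference condition for this sensitivity is having cerebellar disease. The condition that the scale screens for is CCAS. A patient without CCAS whom the scale correctly passes still sits in the denominator and counts as a missed case.

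Two things are at stake. First, a reader may take the figure as the share of CCAS cases that the scale detects, which the study does not measure. Second, the figure feeds a decision. A German cohort with less CCAS would fall short of the US values even with a faithful translation, and the planned response could loosen cut-offs that were sound. A more severely affected cohort could reach the US values and hide a weak translation. One difference from the US cohort is documented: the Perspective section states an interest in focal lesions and notes that the US study tested few such patients.

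**Working it through.** **Inputs from the article (Background):** 39 patients and 55 controls in the US validation; sensitivity 95/82/46%; selectivity 78/93/100%.

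**Step 1, reproduce the US figures.** With all patients or all controls as denominator:
- 37/39 = 94.9%, 32/39 = 82.1%, 18/39 = 46.2%
- 43/55 = 78.2%, 51/55 = 92.7%, 55/55 = 100%

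All six agree with the stated values. The US sensitivities are therefore consistent with positive rates among all cerebellar patients.

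**Step 2, what the figure contains.** Let p be the share of patients who truly have CCAS, Se the true sensitivity for CCAS, and f the positive rate in patients without CCAS. Then

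reported figure = p × Se + (1 − p) × f.

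The documents give neither p nor Se. For f, I assume that 1 − selectivity in controls carries over to CCAS-free patients.

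**Step 3, the best possible scale.** Set Se = 100% and solve for the p at which the reported figure equals the US value, p = (US value − f)/(1 − f):
- possible: (0.95 − 0.22)/0.78 = 0.936
- probable: (0.82 − 0.07)/0.93 = 0.806
- definite: (0.46 − 0)/1 = 0.46

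Below these CCAS frequencies, a scale that misses no CCAS case still falls short of the US value. The result for probable CCAS is not very sensitive to f: with f = 0 the threshold is 82%, and with f = 22% it is (0.82 − 0.22)/0.78 = 76.9%.

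**Step 4, same test, different case mix (probable CCAS, f = 7%).** Se and p are assumed.

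| Assumed p | Se = 90% | Se = 80% |
|---|---|---|
| 90% | 81.7% | 72.7% |
| 80% | 73.4% | 65.4% |
| 70% | 65.1% | 58.1% |

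For example, 0.80 × 0.90 + 0.20 × 0.07 = 0.734. With Se = 90%, each 10-point change in p moves the figure by 10 × (0.90 − 0.07) = 8.3 points.

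**Step 5, the cost of forcing a match.** At p = 70% and Se = 100%, reaching 82% requires f = (0.82 − 0.70)/0.30 = 40%. Cut-offs would have to flag four in ten CCAS-free patients.

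**Step 6, whether the external criterion resolves it.** The construct-validity step covers at least 20 patients and compares two percentages. If 16 of 20 are positive by each method, the percentages are equal. The four negatives may be the same people (20/20 = 100% agreement) or entirely different people (12/20 = 60%). Equal percentages therefore do not give Se.

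**The case against.** The strongest defence is that the definition is stated openly, follows the US study, and fits the primary aim as the Perspective section words it, which is to tell patients from controls. Comparability requires the same definition. This stands: the figure is valid for patient-versus-control discrimination. It does not make a positive rate transferable between cohorts of different make-up, nor turn it into sensitivity for the condition being screened.

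The article also admits that "as yet there are no standard criteria to diagnose CCAS based on detailed neuropsychological testing". That remark is attached to construct validity and does not qualify the sensitivity figure. It is a reason not to claim sensitivity for CCAS.

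The plan does analyse cer-pure against cer-plus, looks at single tests before changing cut-offs, and collects BARS, which "will be used to enable direct comparison with the original US-American validation study". Finer stratification may be set out in a fuller document. The stated comparison that leads to recalibration, however, is of the overall figure, and no other definition is given for the single tests.

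A reader might infer more than the documents support:
- *The figure simply measures how common CCAS is.* It does not. The formula shows three components.
- *The German design changes the cer-pure/cer-plus ratio from the US cohort.* The US split is not given. Only the focal-lesion contrast is documented, and no focal quota is set.
- *Only selectivity should count as evidence on cut-offs.* A translation that made items too easy would raise selectivity and go unnoticed. Controls are screened for neurological and psychiatric disorders, not for CCAS.
- *The study cannot validate anything.* It can validate discrimination from healthy controls, and the construct-validity step adds limited further evidence.

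**Conclusion.** The point holds in this form. What the plan calls sensitivity is the positive rate among all enrolled cerebellar patients. It supports discrimination from healthy controls and is not sensitivity for CCAS. Because it depends on case mix, a crude comparison with 95/82/46% can start and steer cut-off changes for reasons unrelated to the translation.

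The size is illustrative. The threshold of about 81% for probable CCAS assumes perfect detection and that US selectivity applies to CCAS-free patients. The 82/73/65% series also assumes 90% true sensitivity and CCAS frequencies of 90, 80 and 70%. None of these frequencies comes from the documents, and the agreement of 82% with the US value follows from the inputs chosen. It is not evidence that 90% of the US patients had CCAS. The change is worth making before the data are analysed, but the point does not undermine the study as a whole.

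**What to change.** - In the abstract (Methods) and in Data analysis, call the quantity the proportion of cerebellar patients classified as possible, probable or definite CCAS. Describe it as patient-versus-control discrimination and state that it is not sensitivity for CCAS.
- Report it by cer-pure/cer-plus, by degenerative/focal, and by BARS severity.
- In Data analysis, state that cut-offs will not be changed merely because the crude rate lies below the US value. First check whether case mix or severity explains the shortfall, and read it together with selectivity in controls and the item-level results.

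Formal standardisation to the US mix is not needed. It would require US stratum data that the article does not give.

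The cost is a few sentences and some extra tabulation from data already planned. The downside is a less favourable claim, since sensitivity for CCAS is no longer asserted.
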